### Sample size

Sample size estimates are based on the numbers of participants needed to detect differences in proportions of participants in intervention and control groups:

1) Participating in physical activity (defined as reaching the national target recommendations of five sessions of 30 minutes or more of at least moderate activity per week).

2) Self perceived health as measured by the EQ-5D index, from which meanQALY scores and the incremental cost-effectiveness ratio will be calculated.

Under individual randomisation, sample size calculations for a small effect size (0.3) [61] equivalent to a mean difference of 0.05 in the EQ-5D index in general community samples requires 176 participants per study group [62]. Published evidence of participants in a cluster randomised trial of physical activity promotion showed the proportions of participants achieving the same recommended targets for physical activity to be 14.6% (intervention subjects) vs. 4.9% (control subjects) [63]. A total of 215 participants in each study group are required to detect this difference between study groups with 90% power (5% 2-sided significance). Current plans seek a 1% increase in the number of people achieving the physical activity target of five sessions of 30 minutes or more of at least moderate activity per week, year on year [1].

Data from 24 general practices in the British Regional Heart study suggested that an intra-class correlation coefficient (ICC) not exceeding 0.02 was appropriate for physical activity outcomes among middle aged men, but this study aimed to represent the full range of cardiovascular disease prevalence across Britain and the range would probably be less in the proposed study as it is less geographically dispersed [64]. Also ICCs collected for a range of variables in primary care settings have typically averaged 0.01 [65].

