Based on an intra class correlation coefficient of 0.01 the design effect would be 1.31, because 32 participants will provide data per practice (see next paragraph). If 215 participants per arm are required (before allowing for attrition) for an individually randomised design (90% power, 5% 2-sided significance), 282 per arm would be required for the clustered design. Allowing for 30% attrition, this equates to 403 per arm. The sample size is based on detecting differences between each intervention (exercise programme) and the control arm, and there is unlikely to be enough power to detect modest differences in outcome between the two intervention arms.

Assuming an average practice size of 6000 patients, 15% (900) of whom are aged 65 and over [66] and a random 1 in 2 sample (ratio will vary according to the practice size) of patients are approached to take part in the study, 600 patients aged 65 and over would be approached. Assuming that approximately 45 of these patients per practice agree to participate, and allowing for an attrition rate of 30%, outcome data would be obtained on 32 participants per practice.

It is expected that all or most patients in each practice will be invited to join the trial. In larger than average practices, however where the patient list is very large, a stratified random sample of 600 patients will be drawn. Response rates from each practice will be recorded.

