### Statistical methods

Characteristics of participants and practices will be compared descriptively at baseline. Comparisons between treatment arms will be made using random effects models to allow for clustering between practices. Linear regression models will be used for continuous outcome variables, logistic models for binary outcome variables (in particular the primary endpoint, namely attainment of recommended exercise level at 12 months after the intervention), and Poisson or negative binomial models for data on rate of falls. The assumptions for using each model will be checked and analyses adjusted accordingly. All analyses will be undertaken, adjusted (a) for variables used for minimisation (centre, deprivation and practice size), (b) for baseline values of the outcome measure, and (c) for baseline variables which differ to a clinically significant extent between groups. Differential effects of the intervention by age, sex and baseline activity levels will be assessed for the primary outcome measures by adding terms for the interaction between age, sex and baseline activity levels and treatment arm to the regression models.

Multilevel models will be applied to take account of clustering at the practice level (applicable to all arms of the study) and practitioner effects which will apply to differing extents in the OEP arm (due to the effectiveness of different PSIs) and FaME arm (due to the effectiveness of different PMs). Analyses as recommended by Roberts [70] and Walwyn and Roberts [71] (2009) will be applied for this purpose.

While the primary endpoint will be attainment of recommended exercise levels at 12 months, we will investigate the profile of exercise attainment at all time points (0, 6, 12, 18 and 24 months post intervention). We will carry out repeated measures analysis using generalised estimating equations which account for the intra-participant dependency of the repeated measures. In particular we will investigate evidence for differences in effect of the interventions at the different time points.

As the study consists of two intervention arms and one control arm, primary analysis will consist of comparing each intervention group with the control group. No formal adjustment of p-values will be made, since the sample size has been specifically designed to test each intervention separately.

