The economic analysis will adopt standard techniques of economic appraisal [72]. The measure of effectiveness will be mean differences in QALY scores at the end of follow up after adjustment for baseline values, estimated in an analysis of covariance. If statistically significant differences between groups are found, incremental cost effectiveness ratios will be calculated to show the extra cost incurred per QALY gained. Comparisons will be conducted between the usual care group and each type of exercise programme, and between the two interventions, using group means of follow-up QALY values after adjusting for baseline levels. The impact of uncertainties in the estimation of costs and outcome variables will be explored using one way and probabilistic sensitivity analysis. Bootstrap methods will be used to represent uncertainty of estimates, either for constructing confidence intervals or probability curves.

Sensitivity analyses will investigate the cost-effectiveness of the interventions for people with different levels of physical activity, health status and health related quality of life at baseline. Secondary cost-effectiveness analyses will be conducted using physical activity and other outcomes as the measures of effectiveness.

Missing outcome data will be assumed to be "missing at random" (MAR), conditional on key predictors of "missingness" (in particular baseline values of the response variable, treatment arm, and measures of compliance post randomisation) Multiple imputation of outcome variables will be carried out using these predictors of "missingness" [73]. A further sensitivity analysis will be carried out where all who do not report their exercise levels will be assumed to be non-exercisers.

The full analysis set will comprise all randomised participants for whom one post-baseline assessment of the primary outcome measure is available. The per-protocol set will comprise all randomised participants who are deemed to have no protocol violations. CACE analysis will be carried out [74].); this seeks to estimate the difference between compliers in the intervention groups with those who would have complied in the non-intervention group. The safety set will be all randomised participants who undertake at least one OEP session or FaME class.

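### Imputation variables are chosen as predictors of missingness, so the planned arm-by-age, arm-by-sex and arm-by-baseline-activity interactions would be pulled towards zero if tested on data imputed from those variables as main effects

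*Protocol article*

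**What the plan says.** All the analysis text is in the Statistical methods section of the protocol article.

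- **Effect modification.** Differential effects on the primary outcome measures will be assessed by "adding terms for the interaction between age, sex and baseline activity levels and treatment arm to the regression models".
- **Missing data.** Outcomes are assumed missing at random given key predictors of missingness, "in particular baseline values of the response variable, treatment arm, and measures of compliance post randomisation". Then "Multiple imputation of outcome variables will be carried out using these predictors". The form of the imputation model, any product terms, and whether imputation is done by arm are not stated.
- **Analysis set.** The full analysis set is "all randomised participants for whom one post-baseline assessment of the primary outcome measure is available".

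The Sample size section gives the planning attrition: "Allowing for 30% attrition, this equates to 403 per arm". It sizes the trial for each exercise programme against usual care and states no power for any interaction.

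**The concern.** The two statements apply different criteria to the same outcome. The imputation variables are chosen because they predict who is missing. An imputation model must also contain the terms of the analysis that it feeds. Age and sex are not among the named variables. Baseline activity is there, as the baseline value of the response, but its product with arm is not. Records imputed from these variables as main effects carry no direct modification by age, sex or baseline activity. An interaction fitted to the completed data then blends the observed records, which show the true modification, with imputed records that show none.

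The error runs one way, towards no difference between subgroups. These questions matter here. Secondary objective (1) asks about benefit in people starting at various activity levels, the economic sensitivity analyses look at baseline activity, and the Discussion expects already active people to be more likely to volunteer.

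**Working it through.** **1. The plan's own figures.** Inputs from the Sample size section: 14.6% v 4.9%, 90% power, 5% two-sided, ICC 0.01, 32 participants per practice, 30% attrition.

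- Mean proportion = (0.146 + 0.049)/2 = 0.0975; difference = 0.097.
- n = [1.96·√(2 × 0.0975 × 0.9025) + 1.2816·√(0.146 × 0.854 + 0.049 × 0.951)]² / 0.097² ≈ 194.5, i.e. 195. With continuity correction, 215, as stated.
- Design effect = 1 + 31 × 0.01 = 1.31; 215 × 1.31 = 281.7, i.e. 282.
- 282/0.70 = 402.9, i.e. 403. The plan's figures reproduce.

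**2. Closed form for the interaction.** Let f be the share of analysed outcomes that is imputed, and suppose the imputation model omits the interaction.

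- Estimate ≈ (1 − f) × complete-case estimate.
- Rubin variance ≈ (1 + f) × V, where V is the variance with no missing data. The complete-case variance is V/(1 − f).
- The test statistic is therefore r = √[(1 − f)/(1 + f)] times its complete-case value.
- Power = Φ(λ − 1.96/r), where λ is the complete-case noncentrality (1.96 + 0.84 = 2.80 for 80% power).

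Worked case, f = 0.30: r = √(0.70/1.30) = 0.734; 1.96/0.734 = 2.67; Φ(2.80 − 2.67) = Φ(0.13) = 0.55.

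| Share imputed | Estimate retained | r | Power if complete-case is 90% | 80% | 50% |
|---|---|---|---|---|---|
| 10% | 0.90 | 0.905 | 86% | 74% | 42% |
| 15% | 0.85 | 0.860 | 83% | 70% | 37.5% |
| 20% | 0.80 | 0.816 | 80% | 66% | 33% |
| 30% | 0.70 | 0.734 | 72% | 55% | 24% |

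**3. Simulation check.** The setting was 403 per arm, logistic imputation and analysis, 20 imputations, Rubin's rules, 1,500–2,000 replicates, missingness completely at random within cells, and no clustering. The interaction log odds ratios (0.6 to 2.0) are assumptions, because the protocol gives none.

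- Main effects only, 30% imputed: estimate 0.63–0.72 of the complete-case value.
- Arm by sex at 4.9%/14.6%, 30% imputed: power 85% to 55%, 58% to 28%, 34% to 12%, 15% to 3%.
- Adding sex as a main effect only: ratio 0.70–0.72, so no repair.
- Adding sex and its product with arm: ratio 0.99–1.01; power 57% v 59% and 83% v 83% complete-case.
- Arm by baseline activity, named variables only but imputed within arm: ratio 0.99–1.00; power 58% v 60%.

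**4. Role of compliance.** Compliance is a named predictor and can carry modification into the imputed values. The table gives the ratio of the imputed to the complete-case estimate for arm by sex.

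| How the modification acts | 15% imputed | 30% imputed |
|---|---|---|
| Wholly through compliance | 0.99 | 0.98 |
| Partly | 0.92 | 0.83 |
| Not at all | 0.84 | 0.68 |

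**The case against.** The strongest reply is that the protocol does not state an imputation model. The named predictors are introduced as examples, and the remaining terms of such a model are commonly left to the analysis plan. Nothing excludes age, sex, product terms or imputation within arm. Compliance with a programme has no direct counterpart in usual care, which makes handling each arm separately plausible; that alone would remove the shrinkage for baseline activity. The text also does not say that the interaction tests use imputed data. It follows the imputation sentence with a further sensitivity analysis, so imputation may itself be only a sensitivity analysis.

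Most of this stands, and it makes the harm conditional. It does not make the stated criterion adequate. The list is open, but the class it illustrates is predictors of missingness. An analysis plan that follows that criterion faithfully has no reason to add an arm-by-sex term, and would add age or sex only if they predicted dropout.

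A reader might infer that the subgroup effects will shrink by 30% and lose a third to a half of their power. The documents do not support that. The 30% is planning attrition, and people with no post-baseline assessment fall outside the full analysis set, so the share imputed within it is probably lower. A relative loss of a third to a half fits only complete-case power of about 50–80%. With 30% imputed, the loss is 20% at 90% power (90% to 72%) and 73% at 15% power (15% to 4%).

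**Conclusion.** The point holds as a conditional weakness. The criterion for choosing imputation variables does not cover the interactions that the same section commits to testing. The bias towards zero needs two things that the protocol leaves open: the named predictors enter as main effects, and the interaction models are fitted to the imputed data. If both hold, shrinkage is about 10–15% with 10–15% imputed and about 30% with 30% imputed, less so far as modification works through compliance. For baseline activity only the product with arm is unnamed. The power figures rest on assumed interaction sizes and ignore clustering. It would go too far to infer that the trial's main result is at risk: the primary arm comparisons are not shown to be affected, and no power was claimed for the interactions.

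**What to change.** In the missing-data paragraph of Statistical methods, state that outcomes will be imputed separately within each trial arm. The model should keep the baseline value of the response, and compliance where it is defined, and add age, sex and baseline activity. Every interaction to be tested is then in the imputation model. The named predictors should stay, because the missing-at-random assumption for the main comparisons rests on them.

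Alternatively, state that the interaction tests use observed data only. That avoids the shrinkage but gives up the use of compliance to explain missingness in those tests.

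Either change is one sentence, needs no new data and uses standard software. One practical caution applies to imputing within arm: at the planning rate the usual care arm would have about 0.049 × 282 ≈ 14 observed events, so the fit of its imputation model should be checked.

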### Outcome measures

The primary and secondary outcome measures have been chosen to reflect the needs of participants (e.g. functional outcomes, falls, confidence, quality of life, participant costs), of commissioners of exercise services in primary care and policy makers (e.g. physical activity, falls, NHS costs).

The primary outcome will be the proportion reaching the recommended physical activity (PA) target of at least 30 minutes of activity of moderate intensity on at least 5 days each week, measured using the CHAMPS, PASE and PHONE_FITT questionnaires. While measures will be taken at 0, 6, 12, 18 and 24 months after the intervention, our primary analysis will be of 12 month data, as this is the time when the effect of the intervention is expected to be maximal, as seen in a previous evaluation of the OEP in New Zealand [37].

The secondary outcomes will include:

(1) The direct health benefits: i.e. functional and psychological status, the rate of falls (the major safety outcome measure), the number and nature of falls, and fear of falling,

(2) Stage of change, self-efficacy for exercise and physical self-perception (self-esteem relative to the physical domain), which includes measurement of perceived importance (the degree to which participants value their physical condition, body image and physical strength) to inform predictors of exercise adherence and continuation, and participants' judgement of the value or importance of physical activity,

(3) Health - related quality of life and Quality adjusted life years (QALYs) [38],

(4) The NHS and private (participant) costs of each exercise programme, and possible cost offsets, identified from a comparison of health and social service utilisation of participants in all groups during the study period.

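### The full analysis set excludes randomised participants who never return a follow-up assessment, and this is not reconciled with the planned imputation or the non-exerciser sensitivity analysis

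*Protocol article*

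**What the plan says.** All the relevant text is in the protocol article.

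- **Analysis set** (Statistical methods): "The full analysis set will comprise all randomised participants for whom one post-baseline assessment of the primary outcome measure is available". The other sets named there are a per-protocol set and a safety set.
- **Imputation** (Statistical methods): missing outcomes are taken as missing at random (MAR) given, in particular, the baseline value of the response, treatment arm and "measures of compliance post randomisation". Then: "Multiple imputation of outcome variables will be carried out using these predictors".
- **Sensitivity analysis** (Statistical methods): "A further sensitivity analysis will be carried out where all who do not report their exercise levels will be assumed to be non-exercisers".
- **Time point** (Outcome measures): "While measures will be taken at 0, 6, 12, 18 and 24 months after the intervention, our primary analysis will be of 12 month data".
- **Primary comparison** (Statistical methods): each exercise arm is compared with usual care in a random-effects logistic model, adjusted for the minimisation variables, the baseline value of the outcome and baseline variables that differ to a clinically significant extent. No analysis set is named for it.
- **Attrition** (Sample size; Discussion): 30% is allowed for, and limited retention is listed among the anticipated problems.
- **Blinding** (Concealment of allocation; Blinding): allocation is disclosed once a practice's participants are all recruited. After that, neither participants nor outcome assessors are blind.

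**The concern.** A randomised participant who returns no follow-up measure of physical activity falls outside the full analysis set. That is selection on a post-randomisation event. The people lost this way are unlikely to be a random subset. The exercise arms carry a 24-week commitment that usual care does not, and the Contamination paragraph accepts that usual-care participants may be disappointed. Loss could therefore differ between arms, in either direction.

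The exclusion is also unnecessary on the plan's own terms. Baseline assessment comes before allocation is disclosed, so the baseline value and arm should be known for everyone randomised. Compliance in the exercise arms is recorded by participants, mentors and instructors, not through the follow-up questionnaires. None of the named imputation predictors requires a post-baseline outcome.

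At stake is whether the primary contrast keeps the protection of randomisation, and whether the one analysis designed for pessimistic drop-out includes the people it is most needed for.

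**Working it through.** **1. The plan's own figures.** Inputs from Sample size: 14.6% v 4.9%, 90% power, 5% two-sided, ICC 0.01, 32 participants per practice with data, 30% attrition.

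- Two-proportion formula: 195 per arm without continuity correction, 215 with it. The stated 215 reproduces.
- Design effect: 1 + (32 − 1) × 0.01 = 1.31. Then 215 × 1.31 = 281.65, so 282.
- Attrition: 282 / 0.70 = 402.9, so 403.

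All three stated figures hold. Planned attrition is 0.30 × 403 ≈ 121 per arm. This is loss of outcome data, so it serves as a planning ceiling for those never assessed.

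**2. Who is handled by which analysis.**

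| Participant | In full analysis set? | Imputed if imputation uses that set? | Counted as non-exerciser? |
|---|---|---|---|
| Assessed at 12 months | Yes | Not needed | Not needed |
| Assessed at another time, missing at 12 months | Yes | Yes | Yes |
| Never assessed after baseline | No | No | Only if that analysis uses all randomised |

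The third row is the problem. The text does not settle its last cell.

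**3. Bias under the plan's own MAR assumption.** The plan lets missingness depend on compliance. The primary model adjusts for baseline values and minimisation variables but not for compliance. Suppose loss in an exercise arm is concentrated among poor compliers, and poor compliers are less active at 12 months. Dropping the never-assessed then raises that arm's observed rate, and usual care has no matching selection. Imputation using compliance would correct this, but only for people who are in the imputed set.

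**4. Size, as an assumed range.** The documents do not give the share never assessed or its imbalance. Assume no true effect, a true target rate q in both arms, and everyone excluded below target. If a fraction f is excluded, the observed rate in that arm is q / (1 − f). The two values of q are the control and intervention rates in Sample size. The type I error column is a normal approximation with effective n = 403 / 1.31 ≈ 308 per arm before exclusion.

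| q | Excluded, control v exercise | Observed rates | Spurious difference | Type I error |
|---|---|---|---|---|
| 4.9% | 5% v 15% | 5.2% v 5.8% | +0.6 points | 6% |
| 4.9% | 10% v 20% | 5.4% v 6.1% | +0.7 | 6% |
| 4.9% | 15% v 30% | 5.8% v 7.0% | +1.2 | 9% |
| 4.9% | 10% v 30% | 5.4% v 7.0% | +1.6 | 11% |
| 14.6% | 5% v 15% | 15.4% v 17.2% | +1.8 | 9% |
| 14.6% | 10% v 30% | 16.2% v 20.9% | +4.6 | 26% |
| either | equal | equal | 0 | 5% |

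For example, 0.049 / 0.90 = 0.0544 and 0.049 / 0.80 = 0.0613, a difference of 0.7 points. The planned difference is 14.6 − 4.9 = 9.7 points.

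**5. Can the trial bear a non-exerciser analysis on all 403?** With equal 30% loss and 14.6% v 4.9% among reporters, the rates become 0.70 × 14.6 = 10.2% and 0.70 × 4.9 = 3.4%, a difference of 6.8 points. With a design effect of 1 + 44 × 0.01 = 1.44 for 45 per practice, power is about 89%. Completers give about 93% computed the same way, without continuity correction.

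**The case against.** **No contradiction is stated.** A reader might infer that the set contradicts the imputation and the non-exerciser rule. It does not: imputation can run inside the set for people missing only the 12-month measure, and the non-exerciser rule is already a sensitivity analysis and is not tied to this set. This stands. The passages are unreconciled rather than contradictory.

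**The primary analysis is not expressly tied to this set.** Also correct. It is the natural reading, because the name implies it and the other two sets are per-protocol and safety, but it remains an inference.

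**The imputation model may be sound.** A reader might infer that one pooled model is planned, with compliance undefined in usual care and practice left out. The text supports neither. The predictors are introduced as particular examples, arm is among them, and the section commits to modelling practice-level clustering. Such detail can properly sit in an analysis plan.

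**The bias may be small, and the fix only partly matches the illustration.** The set excludes only people with no assessment at any of five time points, the first being the 24-week assessment with functional tests, so the share is probably below 30%. At the 4.9% rate, modest imbalance costs under one point. The illustration is also missing not at random: imputation by arm alone would fill in each arm's observed rate and leave the difference in place. Both points stand. Imputation repairs loss that depends on compliance and baseline activity; the non-exerciser analysis on all randomised covers the illustrated case.

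**It could be left to the full protocol or analysis plan.** This does not stand for the set itself. The article fixes a restrictive definition; it is not silent.

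**Conclusion.** The point holds as a fault in a stated rule. The full analysis set is conditioned on a post-randomisation event without need, and its relation to the imputation and the non-exerciser analysis is left open. If the main comparison uses it, loss that differs by arm and depends on compliance biases the contrast even when the plan's MAR assumption is true.

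The size is uncertain: roughly half a point to two points for a 10-point imbalance in exclusion, and up to about 4.6 points for 10% v 30% at the higher target rate. This rests on assumed exclusion shares, on everyone excluded being below target, and on no true effect. Under those conditions equal exclusion gives no bias. The figures are not a forecast, and nothing in the documents shows that a large imbalance is expected.

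**What to change.** 1. Define the full analysis set as all randomised participants, analysed in their practice's allocated arm. The natural exception is data withdrawn at a participant's request, as the Withdrawals section allows.
2. State that the primary 12-month comparison uses this set.
3. Run the multiple imputation on it, with compliance used within the exercise arms and practice kept in the imputation model.
4. State that the non-exerciser sensitivity analysis, which addresses loss that is not at random, is also run on all randomised participants.
5. Keep the set requiring one post-baseline assessment as a sensitivity analysis.
6. Report, by arm, how many were never assessed after baseline, so that readers can place the trial within the range above.

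The cost is one definition, a few sentences on missing data and slightly more programming. The 403 per arm is unchanged. The change should be settled before the statistician is unblinded.
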